### **Statistical analysis**

The Kolmogorov-Smirnov test will be used to determine whether variables will be normally distributed. For continuous variables the study groups will be compared using the mean equality test or, if necessary, the Mann-Whitney U test. The Kruskal-Wallis H-test will be used to compare the two groups. The comparison between two groups and between two samples will be performed using Welch's t test and Fisher's exact test respectively (with Bonferroni's correction). The  $\chi^2$  test and Fisher's exact test will be used for categorical variables. The data obtained will be assessed by means of linear logistic regression analysis in order to evaluate the possible influence of dietary factors and other variables (anthropometric data, glucose and lipid metabolism variables). We will use a generalized linear regression model (GLM) to examine the contribution of demographic, anamnestic and clinical data of children enrolled on the composition of the microbiota. A GLM model will be built and validated using the rms and ResourceSelection packages implemented in R respectively (<http://www.r-project.org/>). Multivariate statistical analysis (Analysis of the Main

[figure not shown]

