## University of Naples “Federico II” - Naples, Italy

a.m. and immediately analyzed at the hospital laboratory of biochemistry for total cholesterol, HDL-cholesterol, LDL-cholesterol, triglycerides, insulin, and glucose. The HOMA-IR will be calculated as: the product of fasting glucose (mg/dl) and fasting insulin ( $\mu$ UI/ml) divided by 22.5.

To detect serum levels of ghrelin and IL-6 specific Human Ghrelin ELISA Kit (Biotechne, Minneapolis, USA) and IL-6 Human ELISA kit (Abcam, Cambridge, UK) will be used, with a detection limit of 9.38 pg/mL and 6.25 pg/ml, respectively.

Peripheral blood mononuclear cells (PBMCs) will be isolated from peripheral whole-blood (3ml) samples using the Ficoll-Paque (GE Healthcare, Uppsala, Sweden) method. For microRNA (miRNA) expression analysis, total RNA will be isolated from PBMCs using the TRIzol Reagent kit (Invitrogen, Carlsbad, CA, USA) and quantified with the NanoDrop 2000c spectrophotometer (Thermo Scientific, Waltham, MA, USA). RNA quality and integrity will be assessed with the Experion RNA Standard Sense kit (Bio-Rad, Hercules, CA, USA). Quantitative real-time PCR analysis of the miR-221 will be performed with the TaqMan miRNA assay kit and the TaqMan gene expression assay kit, respectively (both from Applied Biosystems, Grand Island, NY, USA) according to the manufacturer's instructions. Samples will run in duplicate at 95°C for 15 seconds and 60°C for 1 minute using an ABI Prism® 7900 Sequence Detection System (Applied Biosystems). Data analysis will be performed with the comparative threshold cycle (CT) method and expressed as  $2^{-\Delta\Delta C_T}$ .

[figure not shown]

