## University of Naples “Federico II” - Naples, Italy

### **Sample size**

Considering a possible drop-out of 10%, will be required 27 patients per group (Group 1: n=27; Group 2: n=27) to observe a BMI z-score reduction at least of  $\geq 0.25$  after 6 months of intervention (Power of the study 90%; type 1 error =0.050, 2- tailed test).

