## University of Naples “Federico II” - Naples, Italy

Components, hierarchical clustering, Analysis of the Main Coordinates, etc.) will be used to identify possible groupings of the samples and the variables that allow to explain these subdivisions. All statistical tests will be carried out in the R / Bioconductor environment and using specific software (stats, vegan, made4, rgl, etc.). The relative abundance tables of the microbial species will also be used for correlation analysis with the other quantitative variables available using the psych software in the R environment. The level of significance for all statistical tests will be 2-sided,  $p < 0.05$ . When appropriate, all significance values will be corrected to take into account the effect of multiple comparisons, using the Bonferroni correction. All data were collected in a dedicated database and analyzed by a statistician blinded to patient group assignment, using SPSS version 19.0 for Windows (SPSS Inc, version 14.0, Chicago, IL).

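### Secondary blood outcomes: the plan chooses between raw-scale tests by a normality pre-test and uses neither logs nor the T0 value, which can cost power; the pre-test itself costs little on T6 values

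*Protocol*

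**What the plan says.** The protocol's Statistical analysis section begins with a normality check: "The Kolmogorov-Smirnov test will be used to determine whether variables will be normally distributed". The groups are then compared by a test of means "or, if necessary, the Mann-Whitney U test"; what makes the rank test necessary is not defined. The next two sentences assign the two-group comparison to Kruskal-Wallis and then to Welch's t test, neither tied to the normality result. No transformation is mentioned. None of these sentences brings in the T0 value, although Study Design has the blood outcomes measured at both T0 and T6. The regression models later in the section serve other questions (dietary and other influences, microbiota composition), not an adjusted comparison of the arms.

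Laboratory determinations defines HOMA-IR as "the product of fasting glucose (mg/dl) and fasting insulin" divided by a constant. For miR-221 it says "Data analysis will be performed with the comparative threshold cycle (CT) method and expressed as" 2^-ΔΔCT.

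On software, the section names R and also has the data analysed "using SPSS version 19.0 for Windows (SPSS Inc, version 14.0, Chicago, IL", so the variant of the Kolmogorov-Smirnov test cannot be read from the text.

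The Sample size section says "will be required 27 patients per group (Group 1: n=27; Group 2: n=27", with the dropout allowance worded "Considering a possible drop-out of 10" per cent. Its power statement, "Power of the study 90%; type 1 error =0.050, 2- tailed test", concerns BMI z-score only.

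**The concern.** HOMA-IR is a product and fold change is an exponential, so differences in both are naturally multiplicative and right skew is plausible. Insulin, triglycerides and ghrelin may behave in the same way. On the raw scale a few high values can dominate the variance.

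The protocol gives no reference mean or SD for the normality test, so both must be estimated from the sample. With standard Kolmogorov-Smirnov tables that makes the test very conservative, and with about two dozen children per arm it would pass much skewed data as normal. Where it does reject, the fallback is a rank test on the same raw values, still without the T0 value.

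At stake is a missed proportional effect of butyrate on the metabolic and miR-221 outcomes. False positives are not the issue.

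**Working it through.** **Inputs.** From the protocol: 27 per group and 10% dropout, so 27 × 0.9 = 24.3, about 24 evaluable per arm (conversely 24 / 0.9 = 26.7, rounded up to 27). The protocol states no figure for the normality test and no SD, skewness, T0-T6 correlation or power for any secondary outcome, so there is no figure of its own to reproduce here. Assumed: log-normal outcomes with log-SD 0.35 to 1.0 (one PCR cycle is ln 2 = 0.69), and T0-T6 correlation r = 0.5 to 0.7 on the log scale.

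**Step 1: how often the gate fires.** At n = 24 the standard 5% critical value is D = 0.269. With fitted mean and SD the correct (Lilliefors) value is 0.176. Used with the standard value, the test rejected truly normal data in 0.0% of 20,000 samples. Rejection per arm for log-normal data:

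| log-SD | uncorrected, n = 24 | uncorrected, n = 27 | Lilliefors, n = 24 | Lilliefors, n = 27 |
|---|---|---|---|---|
| 0.4 | 0.9% | 1.2% | 28% | 32% |
| 0.5 | 2.1% | 2.9% | 41% | 45% |
| 0.6 | 4.9% | 6.0% | 53% | 57% |
| 0.7 | 8.8% | 11.5% | 64% | 69% |
| 1.0 | 28.8% | 35.8% | 87% | 90% |

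**Step 2: cost of the gate on T6 values.** The rule simulated is Welch's test on raw values unless the normality test rejects in either arm, then Mann-Whitney. This is one reading of the text, not a rule that the protocol spells out. Two arms of 24, effect set to about 80% nominal log-scale power, 10,000 runs:

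| log-SD | log-scale t | Mann-Whitney, no gate | raw Welch, no gate | gated, uncorrected | gated, Lilliefors |
|---|---|---|---|---|---|
| 0.4 | 78% | 76% | 75% | 76% | 77% |
| 0.6 | 79% | 76% | 71% | 73% | 76% |
| 0.8 | 78% | 76% | 66% | 73% | 76% |
| 1.0 | 78% | 76% | 58% | 73% | 76% |

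Against the log-scale t test the gate loses about 1 to 6 points. Type I error of the gated rule stays at 4.5 to 5.7%.

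**Step 3: if raw T0-T6 change is compared.** The effect is the one for which log-scale change has 90% power with 24 per arm. The SD of log change is s√(2(1 − r)), so the log difference is (1.960 + 1.282) × s√(2(1 − r)) × √(2/24). For s = 0.5, r = 0.7 this is 3.242 × 0.387 × 0.289 = 0.36, a ratio of about 0.70. For s = 0.9, r = 0.5 it is 3.242 × 0.9 × 0.289 = 0.84, a ratio of about 0.43. With t quantiles the ratios are about 0.69 and 0.42. Power of the uncorrected gate on raw change (3,000 runs):

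| log-SD | r = 0.5 | r = 0.7 |
|---|---|---|
| 0.35 | 79% | 80% |
| 0.5 | 74% | 76% |
| 0.69 | 63% | 65% |
| 0.9 | 57% | 61% |

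A Lilliefors gate gave 66 to 79% for log-SD 0.5 to 0.9. Across repeated runs and both variants the range is about 57 to 83%. Log-scale change itself gave 89 to 92%.

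**Step 4: log T6 adjusted for log T0.** The residual SD falls from s√(2(1 − r)) to s√(1 − r²). For r = 0.5 the standardised effect becomes 3.242 × 1 / 0.866 = 3.74, and power is Φ(3.74 − 1.96) = 96%. For r = 0.7 it becomes 3.242 × 0.775 / 0.714 = 3.52, and power is Φ(3.52 − 1.96) = 94%. Simulation gave 93 to 97%.

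**Step 5: what drives the loss in step 3.** Mann-Whitney on raw change with no gate reaches only 67 to 83%. At the low end the shortfall from 90% is 90 − 57 = 33 points with the uncorrected gate and 90 − 67 = 23 without any gate, so about 10 points are due to the gate and the rest to the raw-change scale.

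**The case against.** A reader might infer that the normality test is the only protection for skewed outcomes, that it almost never rejects, and that these outcomes will therefore be tested raw and lose power. The protocol does not support this. The section also assigns the comparison to Kruskal-Wallis, a rank test, without condition; because an equally unconditional Welch instruction stands beside it, neither settles what will be done. Near-zero rejection holds only for the uncorrected test with mild to moderate skew. A Lilliefors version rejects often, and even the uncorrected one rejects in 29% of samples per arm at log-SD 1.0. The skewness itself is assumed.

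A reader might also take the 57 to 83% as the price of the gate. It is not: most of the shortfall comes from comparing raw change, which the protocol does not prescribe, and part of the gain to 93 to 97% comes from the baseline covariate. The effects in step 3 are also large; for log-SD 0.5 to 0.9 the ratios of 0.42 to 0.69 are reductions of 31 to 58%, and the protocol states no such target.

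Finally, transformations and covariates for laboratory outcomes are often left to an SAP, and one may exist. Their absence alone would be no finding. What stands is that this protocol does fix something: a normality pre-test as the selector, raw-scale tests after it, and fold change as the scale for miR-221. Those choices are worse than an alternative that needs no new data.

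**Conclusion.** The point holds in a limited form. As written, the section selects between raw-scale tests by a pre-test whose variant is unstated, beside instructions that ignore the pre-test, and leaves out T0 values that are already collected. Under the assumed log-normal model with about 24 per arm, the gate alone costs about 1 to 6 points of power on T6 values. If raw change is compared, power is about 57 to 83% against 90% for log-scale change and 93 to 97% for log T6 adjusted for log T0, with either variant of the gate. Type I error is not harmed, and the primary BMI z-score comparison is not part of this point. The size depends on log-SDs and T0-T6 correlations that the protocol does not give; at log-SD 0.35 the raw-change rule still has about 80%. It is a worthwhile improvement to secondary analyses, not a threat to the trial's validity.

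**What to change.** In Statistical analysis, remove the normality pre-test for the secondary blood outcomes and name one analysis for each:

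- Insulin, HOMA-IR, triglycerides and ghrelin: natural log of the T6 value, with the log T0 value as covariate, reported as the butyrate/placebo ratio of geometric means with its 95% CI.
- miR-221: the ΔCT scale at T6 with the T0 ΔCT as covariate; fold change for presentation only.
- Mann-Whitney as a sensitivity analysis. State that the general Kruskal-Wallis and Welch sentences do not apply to these outcomes.

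The cost is a few sentences and no new data. ΔCT is already available before back-transformation. Effects will be reported as ratios rather than raw-unit differences, and a rule is needed for ghrelin values below the assay's stated limit of 9.38 pg/mL before logs are taken.

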## University of Naples “Federico II” - Naples, Italy

In this context oral butyrate administration in obese children could induce body weight loss, that can be achieved by decreasing energy intake, reducing the consumption or absorption of food, and/or by increasing energy expenditure.

The aim of this study is to evaluate the effects of 6-month oral butyrate supplementation compared to placebo in a cohort of obese pediatric patients in addition to standard care for pediatric obesity treatment.

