## **Aims**

### **Main study outcome**

- To determine the effectiveness on child weight status (BMI z-score reduction)

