## University of Naples “Federico II” - Naples, Italy

collected and reported in a specific clinical chart ([Annex 2.](#)).

The patients and their parents/tutor will be instructed on how to complete a food record ([Annex 3.](#)) for the evaluation of dietary patterns which will subsequently be analyzed by a specific software (Winfood - Medimatica Srl). Compliance with the recommendation regarding physical activity and sedentary behaviors at T6 was assessed by questioning about lifestyle habits ([Annex 4.](#)).

At enrollment (T0) and every month for 6 months (T1, T2, T3, T4, T5, T6) will be evaluated: body weight, height, BMI, weight for age percentile, height for age percentile, BMI for age percentile, waist circumference, blood pressure, eating behavior (3 days food record).

At the baseline (T0) and at the end of the study (T6) peripheral blood sampling will be performed for the evaluation of fasting blood glucose, basal insulin, HOMA-IR index, triglyceride, HDL cholesterol, LDL cholesterol, total cholesterol, ghrelin, and expression profile from PBMCs of miR-221. At enrollment (T0), before the start of interventions, and after 6 months (T6) a stool sample for each patient (3 g) will be collected for the metagenomic analyses of the gut microbiota. All samples will be collected from diapers in sterile plastic tubes and stored at -80°C until analysis.

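### The regression is named as linear logistic for a continuous main outcome, and its covariates, many of them outcomes or possible mediators, are not limited to T0

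*Protocol*

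**What the plan says.** - **Main outcome** (Protocol, Main study outcome): "To determine the effectiveness on child weight status (BMI z-score reduction". It is continuous, and no binary version is defined anywhere in the protocol.
- **Group comparison** (Protocol, Statistical analysis): "For continuous variables the study groups will be compared using the mean equality test or, if necessary, the Mann-Whitney U test". Welch's t test is also named. These tests are unadjusted.
- **Regression** (same section): "linear logistic regression analysis in order to evaluate the possible influence of dietary factors and other variables (anthropometric data, glucose and lipid metabolism variables". The sentence refers to the trial data in general. It names no dependent variable, no treatment term and no time point for the covariates. A separate generalized linear model covers microbiota composition.
- **Timing** (Protocol, Study Design): anthropometry and diet are recorded at T0 and monthly to T6, including "blood pressure, eating behavior (3 days food record". Glucose, insulin, HOMA-IR and lipids are measured at T0 and T6.
- **Role of the same variables**: glucose and lipid parameters are listed under Secondary study outcomes. The Background expects weight loss "that can be achieved by decreasing energy intake, reducing the consumption or absorption of food, and/or by increasing energy expenditure".

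**The concern.** There are two faults in one sentence.

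**The model name.** Read as logistic, the model needs a binary outcome that the protocol does not define. Read as linear, the word logistic is wrong. An analyst cannot carry out the sentence as written.

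**The covariates.** Measured at T0, diet, anthropometry, glucose and lipids are legitimate adjusters. Measured at T6, the same variables are trial outcomes (glucose, lipids), a possible pathway of the treatment (diet), or the components from which BMI z-score is built (weight, height, BMI). The text allows either. A treatment coefficient conditioned on T6 values no longer measures the total effect of butyrate: a real effect can shrink or vanish. Adjusting BMI z-score for T6 weight and height comes close to regressing it on itself.

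**Working it through.** **Inputs from the protocol (Sample size).** "Considering a possible drop-out of 10%, will be required 27 patients per group", "to observe a BMI z-score reduction at least of" 0.25, and "Power of the study 90%; type 1 error =0.050, 2- tailed test". Evaluable per arm: 27 × 0.9 = 24.3, taken as 24.

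**Assumptions.** The 0.25 is read as a between-arm difference; the text does not say. The SD is not stated.

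**Step 1: the plan's own figure.** Without an SD, 27 per group cannot be reproduced, only back-solved. From n = 2·SD²·(1.960 + 1.282)²/0.25² with n = 24:

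SD = 0.25 × √12 / 3.242 = 0.267.

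The t-distribution version gives 0.262. The 90% on the continuous scale is therefore true by construction. Power with 24 per arm at other SDs (t test): 0.81 at 0.30, 0.56 at 0.40, 0.40 at 0.50.

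**Step 2: if the model were logistic.** Suppose a responder is a child whose BMI z-score falls by at least 0.25. This cut-point is an assumption; the protocol has none. With control mean reduction m, the responder rates are Φ((m − 0.25)/SD) on control and Φ(m/SD) on butyrate. Power is computed for a two-proportion comparison with 24 per arm, standing in for a logistic model with treatment only.

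| m | Rates at SD 0.262 | Fisher exact power | Normal-approximation power (SD 0.267) |
|---|---|---|---|
| 0 | 17% v 50% | 0.60 | 0.67 |
| 0.05 | 22% v 58% | 0.63 | 0.70 |
| 0.125 | 32% v 68% | 0.66 | 0.72 |

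Against about 0.90 on the continuous scale, power would be about 0.60-0.72. By the normal approximation, restoring 90% would take 39-43 evaluable per arm for m between 0 and 0.25.

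**Step 3: if T6 covariates entered a linear model with treatment.** Let M be a T6 mediator with within-arm SD 1 that carries a share f of the effect and explains a share R² of within-arm outcome variance:

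M = a·T + e; Y = (1 − f)·0.25·T + b·M + u, with b = √R² × SD and a = f × 0.25/b.

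The adjusted treatment coefficient then targets (1 − f) × 0.25. Simulation: 4,000 data sets per scenario, 24 per arm, SD 0.267. Power without M was about 0.89.

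| f | Target of the estimate | Power, R² 0.25 | Power, R² 0.50 |
|---|---|---|---|
| 0 (unaffected by treatment, as a T0 value is) | 0.25 | 0.96 | 0.99 |
| 0.25 | 0.19 | 0.75 | 0.92 |
| 0.50 | 0.125 | 0.38 | 0.55 |
| 0.75 | 0.06 | 0.12 | 0.18 |
| 1 | 0.00 | 0.05 | 0.05 |

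The simulated mean estimates agree with the target column. The values of f and R² are illustrative; the protocol gives neither. The bias depends on f alone. The power also depends on how much outcome variance the mediator explains, so at f = 0.25 and R² = 0.50 power is not lost (0.92 against 0.89) although the estimate is still biased.

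**The case against.** The strongest reply is that the sentence promises little. Its stated purpose is to look at the possible influence of diet and other variables. It sits apart from the group tests, and nothing presents it as the analysis of the butyrate effect. The odd name may be a slip for linear regression, or for linear and logistic. Covariate timing is commonly left to a statistical analysis plan, which is not at hand. Relating on-study diet to weight change is a reasonable exploratory aim. Lower intake is also only one of the proposed routes, alongside absorption and energy expenditure.

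Much of this stands, and it limits the point. A reader might infer that this regression is the adjusted primary analysis, that BMI z-score will be dichotomised, or that T6 values will be entered. The protocol says none of these things, so the power loss and the bias are conditional. Nor would adjusting for a mediator always cost power, as Step 3 shows.

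What does not fall away is the model name. This is not detail deferred to another document: the protocol names a method, and the name contradicts itself and, if read as logistic, does not suit the main outcome. The covariate list is equally explicit about which variables enter, and those variables are measured on treatment as well as at T0.

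**Conclusion.** The point holds in limited form. The protocol names a self-contradictory model for a trial with a continuous main outcome, and it lists covariates that become outcomes, possible mediators or components of BMI z-score if taken after T0. The unadjusted comparison of the arms is untouched.

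The harm arises only if the regression is used to estimate or explain the treatment effect:
- T6 covariates could bias the estimate towards zero, to 0.125 in place of 0.25 if half the effect is mediated.
- A logistic version would lower power from about 0.90 to about 0.60-0.72.

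The power figures rest on 24 evaluable per arm, a between-arm reading of 0.25, a back-solved SD of about 0.26-0.27 and, for the logistic case, an assumed cut-point at 0.25. With a larger SD, power is already lower on the continuous scale. The bias figure rests on the assumed mediated share. The wording should be corrected, but this does not by itself put the main comparison at risk.

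**What to change.** In the Statistical analysis section:

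1. Replace linear logistic regression with a linear model (ANCOVA) of T6 BMI z-score on treatment group and T0 BMI z-score.
2. Allow few further covariates, such as age and sex, and state that all are T0 values.
3. Report on-treatment diet, glucose and lipid variables as outcomes by arm. If they are related to BMI z-score, do so in an analysis labelled exploratory or mediation, not as adjusters of the treatment effect.

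The cost is a few sentences. All T0 values needed are already collected, so there are no new visits or samples. Covariates unaffected by treatment leave the estimate unbiased and should improve precision. In Step 3 power rose from about 0.89 to 0.96-0.99 when such a covariate explained 25-50% of outcome variance; the actual gain depends on how well the T0 values predict the outcome.

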### **Secondary study outcomes**

- To evaluate glucose metabolism parameters (glycemia, insulinemia, HOMA Index), lipid metabolism parameters (total cholesterol, LDL, HDL and triglycerides), serum levels of the hormone ghrelin and of the proinflammatory cytokine IL-6, and on the expression of microRNA-221;
- To assess dietary and lifestyle habits;
- To assess metagenomic characteristic of the gut microbiota.

[figure not shown]

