## University of Naples “Federico II” - Naples, Italy

### *Study Design*

Quadruple-Blind Randomized, Monocentric, Placebo-controlled Study.

Obese patients related to the Pediatric Section of Department of Traslational Medical Science of the University of Naples "Federico II" will be evaluated for the study.

At the baseline, inclusion and exclusion criteria will be assessed and the aims and methods of the study will be illustrated to parents/tutors and young patients. After obtaining informed consent from the patients and their parents/tutor (Annex 1.), patients will be enrolled and randomly assigned to two group of 6-month intervention.

Group 1: standard care for pediatric obesity + sodium butyrate (20 mg/kg body weight/day)

Group 2: standard care for pediatric obesity + placebo (cornstarch)

The packaging, color, weight, smell and taste of the active product and of the placebo will be identical without indication of group identity or content and will be labeled with a serial number according to the computer-generated randomization list, and thus ensured blind conditions.

Instructions for keeping and maintaining the product will be also providing.

All study subjects will be evaluated by a multidisciplinary team (composed by pediatricians, nutritionists and pediatric nurses experienced in the care of pediatric obesity).

Anamnestic, demographic, anthropometric and clinical data will be

[figure not shown]

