## University of Naples “Federico II” - Naples, Italy

delta CT. MiR-301b will be used as reference miRNA for data normalization.

Stool samples will be collected and immediately frozen at  $-80^{\circ}\text{C}$  at enrolment (T0) and at the end of the study (T6). DNA extraction from fecal samples will be carried out following the SOP 07 developed by the International Human Microbiome Standard Consortium ([www.microbiome-standards.org](http://www.microbiome-standards.org)). DNA libraries will be sequenced on Illumina NovaSeq platform, leading to 2x150bp, paired-end reads.

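### No analysis that the protocol ties to the gut microbiota names the randomised arm or the pre-treatment stool sample

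*Protocol*

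**What the plan says.** The last paragraph of the Background gives the aim of the trial: to "evaluate the effects of 6-month oral butyrate supplementation compared to placebo". Under Study Design, children are "randomly assigned to two group of 6-month intervention". Secondary study outcomes includes the item "To assess metagenomic characteristic of the gut microbiota", with no contrast named.

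Sampling is paired. Study Design provides for collection as follows: "At enrollment (T0), before the start of interventions, and after 6 months (T6) a stool sample for each patient". Laboratory determinations repeats the two time points.

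The Statistical analysis section assigns these methods to the microbiota:

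- a GLM to examine the "contribution of demographic, anamnestic and clinical data of children enrolled on the composition of the microbiota";
- principal components, hierarchical clustering and principal coordinates, which "will be used to identify possible groupings of the samples and the variables that allow to explain these subdivisions";
- correlation of species relative abundances with the other quantitative variables.

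The same section also lists general comparisons of the study groups for continuous variables (a test of equal means, Mann-Whitney, Welch's t test, with Bonferroni correction). It does not say that these apply to the microbiota, or whether they use T6 values or changes from T0.

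**The concern.** In a randomised trial with stool taken before and after treatment, the natural question for this outcome is whether six months of butyrate shifted the microbiota relative to placebo. The one model named for composition has a different purpose: it asks which characteristics of the children go with composition. Ordination and clustering look for structure in the samples, and correlation relates abundances to other measurements. An analyst who follows the text can complete every analysis assigned to the microbiota without estimating the randomised contrast.

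Two things are at stake. Associations with child characteristics could end up standing in for a treatment comparison. And if the general two-group tests are used to fill the gap on T6 values alone, the T0 sample, already collected and sequenced, adds nothing to the precision of that comparison.

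**Working it through.** The protocol states no figure for the microbiota analysis, so there is none to reproduce. The check has two parts.

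**1. What each stated method can deliver**

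| Method in Statistical analysis | Tied to microbiota? | Names arm? | Stated to use T0? | Tests overall composition by arm? |
|---|---|---|---|---|
| GLM on demographic, anamnestic and clinical data | yes | no | no | no |
| Principal components, clustering, principal coordinates | yes | no | no | no |
| Correlation of species abundances | yes | no | no | no |
| General two-group tests | no | yes | no | no (one variable at a time) |

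No row is both tied to the microbiota and a comparison of arms. The section also mentions a comparison between two samples, but it assigns Fisher's exact test to it, which is not a paired T0-T6 analysis of abundances.

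**2. What the T0 sample is worth**

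Inputs: 27 children per group and 10% dropout (Sample size section), so 27 × 0.9 = 24.3, about 24 completers per arm. The within-child correlation r between T0 and T6 of a feature is not in the protocol. It is an assumption here, taken over 0.2 to 0.7.

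Adjusting a T6 feature for its T0 value multiplies the residual variance by 1 − r², and the standard error by √(1 − r²), relative to a T6-only comparison:

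| r | 1 − r² | √(1 − r²) | SE smaller by |
|---|---|---|---|
| 0.2 | 0.96 | 0.980 | 2% |
| 0.3 | 0.91 | 0.954 | 5% |
| 0.5 | 0.75 | 0.866 | 13% |
| 0.7 | 0.51 | 0.714 | 29% |

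If the general tests were run on change from T0 instead, the change-score variance is 2(1 − r) times the T6 variance. Adjustment then multiplies the standard error by √[(1 − r²) / (2(1 − r))] = √[(1 + r)/2]. At r = 0.5 this is √0.75 = 0.866 (13% smaller). At r = 0.7 it is √0.85 = 0.922 (8% smaller).

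These factors measure only the value of the T0 adjustment. The absence of arm from the named methods is a matter of the text and does not depend on r.

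**The case against.** The strongest reply is that the GLM is faulted for a question it never claims to answer. Its stated purpose is association with child characteristics, and such a model beside a group comparison is no error. The group comparison is in the same section: species abundances are continuous variables, nothing excludes them from the two-group tests, and under randomisation even a T6-only test is unbiased. **This stands.** A reader might infer that the protocol permits no arm comparison of the microbiota, and the text does not support that.

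Two other inferences also go too far. One is that the GLM pools T6 samples over arms and so leaves a treatment effect in its residual. The protocol gives neither a time point nor pooling for this model, and if it were fitted to T0 samples, taken before treatment, arm would not matter. The other is that the stool is collected expressly for an arm comparison. The protocol says only that "a stool sample for each patient (3 g) will be collected for the metagenomic analyses of the gut microbiota", and the comparative purpose has to be inferred from the overall aim and the design.

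It can also be said that the predictor list is not closed. The Annex 2 chart, whose title covers anamnestic, demographic, anthropometric and clinical data, has a Group box, and the search for variables that explain the groupings could include arm. This is possible but unstated, and allocation is not ordinarily counted as clinical data of a child.

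Finally, model terms for a secondary outcome are often left to the statistical analysis plan, which is not shown. That would settle the matter if the protocol were silent. It is not: it names the methods and their purposes, and none of the purposes it gives for the microbiota is the treatment effect.

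**Conclusion.** The point holds in a limited form. The protocol's named microbiota analyses describe associations and groupings; none names arm or uses the T0 sample as a baseline. The general two-group tests give a valid but unassigned route for single abundances, and no route to overall composition.

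The loss is one of focus and precision; no bias is shown. The size of the precision loss is uncertain. It is negligible for features that vary widely within a child (2% to 5% of the standard error at r of 0.2 to 0.3) and material for stable ones (13% to 29% at r of 0.5 to 0.7). These figures assume a roughly linear T0-T6 relation on the analysis scale and a similar r in both arms, and they ignore the small cost of estimating the slope with about 24 children per arm.

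The outcome is secondary and the primary BMI z-score conclusion is untouched. The change is worth making because it costs almost nothing.

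**What to change.** In the Statistical analysis section, for the secondary microbiota outcome:

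1. State that the term of interest is randomised arm.
2. Model each suitably transformed T6 feature on arm plus the T0 value of the same feature. Demographic data may be added as further covariates.
3. Test overall composition with a permutation test of arm-by-time that permutes whole children, so that each child's T0 and T6 samples stay together. The vegan package, already listed, can be used.
4. Label the GLM on child characteristics, the clustering and the ordination as descriptive.

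The cost is a few lines of analysis text and code. No new data, samples or software are needed.
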